### Statistical analysis methods

We will use descriptive statistics including frequencies, mean and SD, and median and
interquartile ranges as appropriate to describe the sample characteristics and number
and length of episodes of care. Trajectory of outcomes and costs will be described,
comparing patterns in patients with cancer and without cancer, and contrasting
those with no unmet needs and those with unmet needs. We will compare our data with
existing phase and episode data from the Australian Palliative Care Outcome
Collaboration.^48^ In the Australian
classification, five casemix criteria (phase of illness, problem severity, functional
status and dependency, age, model of care) were found to be most strongly predictive
of resource use. If our analyses demonstrate the same five criteria as most
predictive of resource use, the Australian classification or a refinement of it will
be adopted. If there is disparity, then the data on individual casemix criteria will
be used to develop a new casemix classification, using a recursive partitioning
approach—specifically classification and regression trees^49 50^compared with multivariable regression (figure 1).

**Figure 1 F1:**
[figure not shown]
Data analysis flowchart. CART, classification and regression
trees.

### Qualitative analysis methods

Audio-recordings will be transcribed verbatim and checked for accuracy and entered
into NVivo V.10. Data will be independently coded and analysed by two members of the
research team. We will adopt a similar approach to Pinnock,^51^ undertaking a thematic and narrative analysis of interviews,
exploring how perspectives evolve over time, with detailed attention to patient and
family perspectives on experience of care in each setting and transitions, including
potential interventions (and hence cost levers or other triggers) to influence
changes in settings of care.

### Model development

The distribution of casemix criteria (cost predictors) in the participant population
will be described based on phase of illness, functional status and problem severity,
using parametric or non-parametric statistics, as appropriate. In order to reduce the
number of cost predictors, we will initially use univariate analysis to explore the
association and strength of association between casemix criteria and cost of the
episode of care (quantifying cost by per diem cost, per phase cost and total cost of
episode). We will use generalised linear model (multivariate regression model) to
select variables that will then be applied in a hierarchical manner to form a
branching classification in which each cost driver is incorporated only once.

We will select variables according to how much of the predictive error
(R^2^) each variable predicts and the related P value. After each
bootstrap iteration, we will rank the variables according to these two criteria and
remove the weakest (non-significant) predictor. Variables shown in tables 2 and 3 and the newly created
categorical variable representing ‘model of care’ will be initially
entered into the models and then non-significant predictors removed at each iteration
using a Bootstrap subsampling strategy. We will create dummy variables to enable each
level of phase of illness and model of care (categorical variables) to be assessed
individually. Internal validation will be conducted by using such methods as
bootstrapping or cross-validation to quantify any optimism in the predictive
performance (calibration and discrimination) of the developed classification.

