**Figure 2 F2:**
[figure not shown]
Casemix classification specification.

Multilevel modelling will be undertaken to ensure that both of these steps
will be delivered in this study by determining (1) which casemix criteria are most
strongly associated with clinical outcomes, allowing for clustering at the level of
‘participant’ (where episodes occur in the same individual), at the
level of ‘model of care’ (where care is received according to similar
models), and at the level of ‘site’ (where care is delivered in a
similar way within site), and (2) which casemix criteria are the strongest cost
predictor (including per diem cost, per phase cost and total episode cost).

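### Whether to adopt the Australian classification turns on which variables are selected, not on how well it predicts UK cost, and the selection method is unstable and optimistic at the planned sample size

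*Protocol article*

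**What the plan says.** **Adoption rule (Statistical analysis methods).** The condition is "If our analyses demonstrate the same five criteria as most" predictive. The consequence follows directly: "predictive of resource use, the Australian classification or a refinement of it will" be adopted. If the criteria differ, a new classification is developed by classification and regression trees, compared with multivariable regression.

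**Selection (Model development).** The stated purpose of the first step is to cut down the "number of cost predictors, we will initially use univariate analysis to explore the" association with cost. A generalised linear model then selects variables by how much of the predictive error ("R^2^) each variable predicts and the related P value"). After each bootstrap iteration the variables are ranked on these two criteria, and the instruction is to "remove the weakest (non-significant) predictor". The same section says that the variables of tables 2 and 3 plus model of care are initially "entered into the models and then non-significant predictors removed at each iteration". Phase of illness and model of care go in as dummy variables. Internal validation by bootstrapping or cross-validation is to quantify optimism.

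**Multilevel models (Model specification, after figure 2).** These are to find (1) the criteria most "strongly associated with clinical outcomes, allowing for clustering at the level of" participant, model of care and site. The sentence ends: "similar way within site), and (2) which casemix criteria are the strongest cost" predictor.

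**The concern.** Adopting, refining or replacing the Australian classification is the central decision of phase I. As written, it depends on whether five variable names reappear at the top of a list. The same five criteria could emerge while the Australian classes, with their own cut points, explain little UK cost. A different list could emerge while a classification built on it predicts no better. The Introduction itself doubts that an existing classification transfers between countries.

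The list also comes from a data-driven search. If the search would often return different variables from another sample of the same size, the decision is partly chance. R-squared and P value are both computed on the data being searched, so the fit of the selected model looks better than it will in new patients.

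**Working it through.** **Inputs from the Sample size section.** 450 episodes per setting, 25% incomplete, up to 10% of complete episodes cost outliers, the rule 50 + 8m, R-squared 0.13, 80% power, alpha 5%.

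**Reproducing the plan's figures.**
- Validation: 50 + 8 × 8 = 114 episodes per setting, as stated. The F test with n = 114, m = 8 and R-squared 0.13 has power 0.825, consistent with 80%.
- Development: 3 × 450 = 1350, as stated. Usable episodes per setting are 450 × 0.75 × 0.90 = 303.75, about 304.
- The development m is not given. Back-solved, (303.75 − 50) / 8 = 31.7, so up to 31 predictors.

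**Number of candidates.** Table 2 has 8 + 3 + 4 + 5 = 20 rows. Table 3 has 5 + 4 = 9, but is collected in the validation phase only. Phase I therefore has about 20 rows plus model of care, and more once dummies are counted. A range of 20 to 31 was used.

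**Simulation.** Cost y = Xβ + error. X is normal with common correlation ρ. Five true predictors have equal effects scaled so that β′Σβ = R-squared, and the error variance is 1 − R-squared. Selection is a univariate screen at P < 0.05 or P < 0.20, then backward elimination at P < 0.05. New-data R-squared is 1 − [(1 − R-squared) + (b − β)′Σ(b − β) + b₀²]. Top five means that the five largest |t| in the final model belong to the five true predictors. There were 600 samples per case, so the Monte Carlo standard error at 25% is √(0.25 × 0.75 / 600) = 0.018. Candidate count, correlation, thresholds and effect pattern are assumptions, not protocol figures.

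| R-squared | ρ | Candidates | True five are top five | Apparent R-squared | New-data R-squared |
|---|---|---|---|---|---|
| 0.13 | 0 | 31 | 22–25% | 0.149–0.159 | 0.073–0.077 |
| 0.13 | 0.3 | 31 | 0.3–0.5% | 0.148–0.152 | 0.075–0.078 |
| 0.13 | 0.3 | 20 | 0.5% | 0.143 | 0.082 |
| 0.26 | 0 | 31 | 83–90% | 0.277–0.288 | 0.225–0.229 |
| 0.26 | 0.3 | 31 | 10–11% | 0.284–0.286 | 0.209–0.211 |
| 0.40 | 0 | 31 | 99.5–99.8% | 0.416–0.420 | 0.376–0.382 |
| 0.40 | 0.3 | 31 | 58.5–64% | 0.423–0.425 | 0.367–0.368 |

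Ranges cover the two screening thresholds; the 20-candidate row uses P < 0.20 only. With about 20 uncorrelated candidates the top-five figure at R-squared 0.13 is somewhat higher than with 31, but still a minority of samples.

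**Variations.**
- Unequal effects, R-squared 0.40, ρ = 0.3, 31 candidates: top five in 14%.
- All settings pooled (3 × 303.75, about 911 episodes), R-squared 0.13, ρ = 0.3: top five in 26%, apparent 0.140 against 0.112.
- No univariate screen, 30 candidates, R-squared 0.13: apparent 0.158 against about 0.07, so the screen is not the sole cause.

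**Why resampling must repeat the selection.** At R-squared 0.13, ρ = 0.3 and 31 candidates, apparent R-squared was 0.155 and true new-data R-squared 0.072. A bootstrap with the selected set held fixed corrected it only to 0.132. Repeating selection in every resample gave 0.065.

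**Passages side by side.** Model development both reduces predictors univariately and enters all table 2 and 3 variables, so whether the univariate step is a gate is open. It enters table 3 variables that phase I does not collect. It treats model of care as fixed dummies, whereas Model specification lists it as a clustering level.

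**The case against.** Several stronger readings are tempting, and the document does not support them.

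- **The univariate step is a P-value gate outside the bootstrap.** No threshold is given, and a later sentence enters all variables into the model. The wording needs reconciling; it does not establish a gate.
- **Selection uses P values alone.** R-squared is also used, with ranking over bootstrap iterations. Both measures come from the same data, however, so this does not remove the optimism.
- **Optimism is ignored, or will be measured with selection held fixed.** The article plans to quantify optimism and does not say how. It also plans validation in a new phase II cohort, with refinement on that performance. What remains is that repeating the selection is not stated. Phase II as described tests the classes carried forward, not the option that was passed over.
- **This elimination alone decides adoption.** The rule speaks only of the study's analyses, a multilevel route to the cost predictors exists, and the flowchart in figure 1 is not shown.
- **Clustering is ignored and inflates false positives for model of care.** The clustering clause is attached to clinical outcomes, but multilevel modelling is also named for cost. Any error rate would rest on an assumed intraclass correlation and on a model-of-care variable that is still to be created.

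Two further points count in the plan's favour. Allowing a refinement leaves room for different cut points once the five criteria match, though it does not help when they do not. R-squared 0.13 is the effect size used for sample size, not a forecast of fit, and the results depend strongly on it. The planned comparison with Australian phase and episode data is descriptive and does not test the classes against UK cost.

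**Conclusion.** The point holds in this form. The adoption rule is a match of criteria with no performance test, which can be read directly from the text and needs no simulation. The selection feeding it is unstable and optimistic at the plan's own n and R-squared: with 31 candidates, the true five rank top in at most about a quarter of samples. Over 20–31 candidates, roughly half of the apparent R-squared is lost in new data (0.14–0.16 to 0.07–0.08). This size rests on R-squared 0.13, normal errors, and the assumed candidate numbers, correlations and thresholds. It eases as signal grows, and largely vanishes for the ranking at R-squared 0.40 with equal, uncorrelated effects, but not with correlated or unequal effects. The roles of the univariate step, the table 3 variables and model of care are unsettled and need reconciling.

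**What to change.** 1. Remove the univariate step as a selection gate; keep it as description. Fix the phase I candidate list in advance from table 2 plus model of care, and leave table 3 to phase II.
2. Repeat every selection and tree step inside each bootstrap or cross-validation resample, resampling by patient. Resampling by site is not workable with three phase I hospital sites.
3. Account for participant and site in the cost models, and treat model of care as a fixed predictor only.
4. Decide adopt, refine or build on phase I performance. Compare the R-squared and calibration of the Australian classes with those of the optimism-corrected new tree, against a margin set beforehand. Where UK measures cannot be mapped to the Australian classes, use instead a classification limited to the five Australian criteria. Name the cost measure for this comparison, since the Outcome section lists three.

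The cost is revised analysis wording and some programming. No new data items are needed beyond the model-of-care variable already planned, but mapping to the Australian classes has to be checked. Reported performance will be lower.

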### Sample size

In the development phase, based on standard recommendations for fitting multivariate
models, a minimum of 50+8×m (where m is the number of predictors) is required
to test the hypothesis that the population multiple correlation equals zero with a
power of 80%, alpha=5% and a medium effect size for the regression analysis
(R^2^=0.13).^46^ We estimated a
sample size of 450 episodes per setting (allowing for 25% incomplete episodes and up
to 10% of complete episodes being cost outliers with unusually high or low costs). A
total of 1350 patient episodes across settings is needed.

In the validation phase, again a minimum of 50+8×m (where m is the number of
predictors) is required to test the hypothesis that the population multiple
correlation equals zero with a power of 80%, alpha=5% and a medium effect size
for the regression analysis (R^2^=0.13).^46^ In phase II, the number of predictors reflects the casemix variables,
and needs to be clinically relevant^47^ to
ensure a meaningful casemix classification. We expect the final casemix
classification to contain 5–8 casemix variables, based on the Australian
experience.^13^ We have estimated that data
from 114 (50+(8×8)) episodes of care per setting (hospice, hospital,
community) are needed. Assuming an average of three episodes per participant^15^ in this longitudinal phase, this represents at
least 38 participants per setting. Allowing for 50% attrition, we estimate needing a
total of 228 participants, which will provide about 684 patient episodes. The sample
size will be recalculated and inflated using the design effect based on intraclass
correlation which will be estimated through interim analyses. A total of 300
participants across settings is needed, including extra 25% participants allowing for
intraclass correlation.

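### Predictors are dropped after each bootstrap iteration with no pooling over resamples, so on the natural reading true cost predictors are lost by chance and the selected set depends heavily on the random seed

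*Protocol article*

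**What the plan says.** The Model development section of the protocol article sets two selection criteria, each variable's contribution to R2 and its P value. It then fixes when they are applied: "After each bootstrap iteration, we will rank the variables according to these two criteria and remove the weakest (non-significant) predictor". Two sentences later, the variables of Tables 2 and 3 and the model-of-care variable are to be "entered into the models and then non-significant predictors removed at each iteration", and this is done "using a Bootstrap subsampling strategy".

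The two sentences differ on what leaves the model at each step: one predictor (the weakest, if non-significant) or every non-significant predictor. Neither mentions combining results over resamples before a removal, or letting a removed predictor return. The section does not give the size of a resample, whether it is drawn with replacement, the number of resamples per iteration, or the P-value threshold. Bootstrapping or cross-validation is then named for estimating the optimism of the developed classification.

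**The concern.** Backward elimination gives a reproducible answer when each step uses the same data. Here each step is tied to a bootstrap iteration. If an iteration is one resample, a fresh random draw decides each removal, and nothing described reverses it. A genuine predictor goes if it happens to be weakest and non-significant in one draw, and it faces that risk at every step.

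There is a second, smaller problem. A full-size resample with replacement comes from data in which the coefficient equals the sample estimate, not zero. The model P value within that resample therefore does not test a zero coefficient in the population.

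Objective 1 (Introduction) is to determine the cost predictors. The selected variables form the branching classification. Under Statistical analysis methods, whether they match the five Australian criteria decides between adopting that classification and building a new one. A set that changes with the seed is a weak basis for that decision.

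**Working it through.** **Inputs from the article.** Sample size gives 450 episodes per setting, with allowances of 25% for incomplete episodes and up to 10% of complete episodes for cost outliers. It gives R2 = 0.13 and alpha = 5%, both for the overall regression test. The total reproduces: 450 × 3 = 1350. Usable episodes per setting: 450 × 0.75 × 0.90 = 303.75, about 304. The article states no error rate for the selection procedure, so there is no stated figure to reproduce for that.

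**Assumptions.** 20 candidates, 5 true with equal effects and 15 null; independent predictors; ordinary least squares; 5% two-sided removal threshold; a fresh resample at each step; the predictor with the largest P removed; stop when all that remain are significant. For single-degree-of-freedom terms in one linear model, ranking by P and ranking by the loss in R2 are the same, and the article assesses each category level through its own dummy variable.

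**Step 1: a null predictor, one test.** Given the data, the resample statistic z* is about N(z, 1). Under the null z is N(0, 1), so z* is about N(0, 2).
- P(|z*| > 1.96) = 2[1 − Φ(1.96/√2)] = 16.6%, against 5%. Simulation gave 15.9-16.9%.
- At a 10% threshold the rate is about 24.5%; at 1% it is about 6.9%.
- With 63.2% subsamples drawn without replacement, simulation gave 4.9-5.1%, so there is no inflation.

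**Step 2: a true predictor, one test.** Effect size: 0.13/0.87 = 0.149 in total and 0.149/5 = 0.030 each. The expected z is √(0.030 × 304), about 3.0.
- Original data: Φ(3.0 − 1.96) = Φ(1.04), about 85%.
- Full-size resample: Φ(1.04/√2) = Φ(0.74), about 77%.

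The rest of the loss comes from repeating the test at every step.

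**Step 3: the whole procedure, by simulation under the assumptions above.**

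| Selection | True predictors kept | All five kept |
|---|---|---|
| Original data | 84% | 44-46% |
| One full-size resample per iteration | about 64% | 14-18% |
| One 63% subsample per iteration | about 55% | not tabulated |
| Full-size resample, all non-significant dropped at once | about 50% | not tabulated |
| 50 resamples pooled before each removal | 83% | not tabulated |

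Two runs of the resample rule on the same data gave the same set about 10-18% of the time.

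**Step 4: a second scenario.** Here n = 303, with 8 true predictors (4 weaker, 4 stronger) and 12 null.

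| Selection | Weaker kept | Stronger kept | Null kept |
|---|---|---|---|
| Original data | 80% | 97% | 5.1% |
| Full-size resample | 54% | 85% | 3.8% |
| 63% subsample | 46% | 80% | 1.4% |

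At n = 1350, with effects scaled to hold the power of each test constant, the full-size resample kept 59% and 87%, against 79% and 98% on the original data. Nulls were kept 3.6% against 5.0%. The loss is therefore not a small-sample artefact. This run does not show what a larger sample would do for effects of fixed size.

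**The case against.** The strongest reply is that the article is a condensed account and does not say that an iteration is one resample. It could hold many, with ranking done on pooled results; settings of this kind are often left to an analysis plan, and the flowchart in Figure 1 was not available for this check. That is fair as far as it goes, and the point is conditional on the natural reading. But the text does state a rule, with removal after each iteration, and it words that rule two ways. Pooling many resamples before a removal is not written, and it is in effect the repair.

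A second reply is that other steps protect the result: comparison of regression with trees, multilevel modelling, internal validation, and refinement on phase II data. None of these is described as bringing back a predictor dropped at this stage.

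Third, the size of the loss depends on assumed effects. This stands. R2 = 0.13 is a planning value, and stronger predictors lose less (97% to 85% in the second scenario).

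Three stronger readings are tempting, and the article does not support them:
- **That the final model holds three times too many false predictors.** The 16.6% is a per-test rate that needs full-size sampling with replacement and a 5% threshold, whereas the article speaks of subsampling. Nulls face a fresh test at each step and end up kept about 4% of the time, against 5% on the original data.
- **That a long enough run would remove nearly every predictor.** This needs an iteration count and the absence of any stopping rule; the article gives neither.
- **That the seed matters more than the data.** Heavy dependence on the seed is shown; that comparison is not.

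**Conclusion.** The point holds in conditional form. As written, predictors are removed after each bootstrap iteration without pooling or re-entry, under two different removal rules. If an iteration is one resample, about 64% of true predictors are kept (about 55% with 63% subsamples without replacement), against 84% on the original data, and repeat runs on the same data agree about 10-18% of the time. These figures rest on 304 usable episodes, 20 candidates, 5 equal true effects, total R2 = 0.13 and a 5% threshold. All but the episode count and R2 are assumptions about the selection step, and R2 is borrowed from the sample size calculation. Loss of true predictors appeared under every resampling scheme tried and is the main harm. The invalid P value is secondary: it does not inflate false predictors in the final set and does not arise when subsampling without replacement.

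**What to change.** Reword the Model development section to do one of two things:

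1. Run the whole selection on the original (or imputed) data, with P values computed there, and use the bootstrap to report how often each variable is selected.
2. Pool results over many resamples before any removal, for example by inclusion frequency or by the percentile interval of each coefficient across resamples.

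In either case, state a single removal rule, the threshold, and the resampling scheme and size. Repeat the whole selection inside each bootstrap sample used to estimate optimism, so that the estimate reflects the selection as well as the fit.

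The cost is a wording change and slightly more computing; no new data are needed. The one downside is that the reported selection frequencies will show some predictors as less certain.

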#### Predictors collected from clinicians

In both the development and validation phases, clinicians will record demographic,
clinical and episode start administrative data. Episode end data will be collected
at the end of each episode of care. Casemix data include phase of illness (stable,
unstable, deteriorating, dying), functional status (measured by Australia-modified
Karnofsky Performance Status (AKPS)), dependency (Modified Barthel Index), problem
severity (Integrated Palliative care Outcome Scale—IPOS staff version) and
caregiver needs (table 2). The measures are
available directly from phase of illness (www.pcoc.org.au), AKPS,^40^ Modified Barthel Index^41^ and IPOS (www.pos-pal.org), respectively. Phase of illness will be assessed
daily for people receiving inpatient care and at each face-to-face contact basis
for those receiving community-based care. Other variables including AKPS, Modified
Barthel Index, IPOS staff (and caregiver needs when feasible) will be collected at
the start of episode, end of episode and at change of phase of illness.

**Table 2 T2:** Data from clinicians in both development phase and validation phase

Type of data	Proposed cost predictors
Demographic data	Age
	Gender
	Postcode
	Ethnicity
	Marital status
	Living circumstances
	Need for interpreter
	Setting of care
Clinical data	Primary diagnosis
	Secondary diagnoses
	Comorbidities
Episode start and end data	Episode start date
	Episode end date
	Endpoint of episode (discharged or died).
	Discharge destination, if discharged
Key casemix	Phase of illness at start of episode
	Functional status (AKPS)
	Dependency (Modified Barthel Index)
	Problem severity (IPOS staff version)
	Family/caregiver needs

AKPS, Australia-modified Karnofsky Performance Status; IPOS, Integrated
Palliative care Outcome Scale.

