#### Model of care

Models of care may be a stronger cost driver than patient-level variables.^13 14 16^ Specialist palliative care
services have various configurations of staff, interventions and other
characteristics. Currently, there is no consistent way to define models of
palliative care. A separate, parallel study will be conducted in which
service-level data including the numbers, disciplines and grading of staff, the
nature/duration of their involvement and use of volunteers will be collected to
comprehensively characterise different models of palliative care provision in the
participating sites. With findings from this step, a new categorical variable will
be created representing ‘model of care’ to be included in our
analysis.

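### Selecting phase of illness and model of care level by level makes the surviving levels, and the regression coefficients reported from them, depend on an arbitrary reference level

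*Protocol article*

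**What the plan says.** All of this stands in the protocol article, mainly under Model development.

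- Variables are ranked by how much R² "each variable predicts and the related P value". After each bootstrap iteration the team will "remove the weakest (non-significant) predictor".
- The variables of Tables 2 and 3 and the new model-of-care variable are "entered into the models and then non-significant predictors removed at each iteration".
- The next sentence provides dummy variables so that each "level of phase of illness and model of care (categorical variables) to be assessed" individually.
- The selected variables then form a "branching classification in which each cost driver is incorporated only once".

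Phase of illness has four levels: stable, then "unstable, deteriorating, dying), functional status (measured by Australia-modified" and so on (Predictors collected from clinicians). The levels of model of care are not yet known. A categorical variable will "be created representing ‘model of care’ to be included in our" analysis once a parallel study reports (Model of care). Model specification says that all regression coefficients and the intercept will be presented.

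The article names no reference level, no joint test of a factor, and no rule that keeps the levels of a factor together.

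**The concern.** In a model with an intercept, the coefficient, P value and incremental R² of a dummy all describe the difference between its level and the omitted level. Removing the dummy pools that level with the reference. Two consequences follow without any assumption about the data. Two similar non-reference levels can never be merged with each other alone. And a level can be pooled with a reference that differs from it in cost, if the contrast is imprecise. Ranking on R² as well as P does not help, because the R² of a single dummy depends on the reference too.

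Merging phases may be a perfectly good aim. The difficulty is that this rule merges according to the coding, not according to similarity of cost. Phase of illness is listed among the key casemix variables, and the article says models of care may drive cost more strongly than patient-level variables. Model of care is a newly built variable and has no natural reference. At stake are the levels shown as cost predictors and the coefficients published for them.

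**Working it through.** **Inputs from the article.** Phase has four levels, hence three dummies and four possible references. The development phase plans 450 episodes per setting, less 25% incomplete and then up to 10% of complete episodes as outliers: 450 × 0.75 × 0.90 = 303.75, about 304 usable. The validation phase plans 50 + 8 × 8 = 114 episodes per setting, as stated. The article gives no figure for the selection step itself. The 5% removal threshold used here is an assumption, borrowed from the sample size statement ("power of 80%, alpha=5% and a medium effect size for the regression analysis").

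**Worked example (assumed means and level sizes).** Take 303 episodes, sizes 106/45/107/45 for stable/unstable/deteriorating/dying, and mean costs 0/0.25/0.50/0.75 in SD units. The within-level sum of squares is set to 303, so the residual SD is √(303/299) = 1.0067. Each contrast is t = difference / [1.0067 × √(1/n₁ + 1/n₂)].

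- Stable v unstable: 0.25 / (1.0067 × 0.1779) = 1.40, P = 0.164.
- Stable v deteriorating: 0.50 / (1.0067 × 0.1370) = 3.62, P = 0.0003.
- Unstable v deteriorating, and dying v deteriorating: 0.25 / (1.0067 × 0.1777) = 1.40, P = 0.163 each.

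Backward elimination of single dummies then gives:

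| Reference | Dummies that survive | Levels merged |
|---|---|---|
| Stable | deteriorating, dying | stable + unstable |
| Unstable | deteriorating, dying | stable + unstable |
| Deteriorating | stable | unstable + deteriorating + dying |
| Dying | stable | unstable + deteriorating + dying |

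The same data and the same initial fit yield two different groupings. The joint F test on 3 df gives P = 0.00007 and R² = 0.070 under all four references.

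**Simulation, main scenario (assumed).** n = 304; shares 30/20/35/15%; mean costs 0/0.35/0.25/0.70 SD. The between-level variance is (0.20 × 0.35² + 0.35 × 0.25² + 0.15 × 0.70²) − 0.2625² = 0.1199 − 0.0689 = 0.0510, so phase R² = 0.0510/1.0510 = 0.05. Results:

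- Grouping differs between stable and deteriorating as reference: about 54% of data sets.
- Grouping differs between at least two of the four references: 98%.
- At least one phase dummy survives: 96%, 98%, 98% and 96% under the four references.
- Phase is kept under some references and dropped under others: about 5% to 6%.
- The joint 3-df test keeps phase in 93% to 95%, depending on the run.

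**Sensitivity to the assumed means.**

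| Assumed means (SD) | n | Any two references differ |
|---|---|---|
| 0/0/0/0.8 (only dying raised) | 304 | 100% (stable v deteriorating: about 7%) |
| 0/0.5/1/1.5 | 304 | 44% |
| 0/1.0/0.7/2.0 | 304 | 54% |
| no phase effect | 304 | 18% |
| three other moderate patterns | 303 | 96% to 99.6% |
| the same three patterns | 114 | 65% to 85% |

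In those three patterns the joint test gave the same P value under every reference in every data set.

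**The case against.** **The article never says outright that single dummies are deleted.** Its selection sentences speak of variables and predictors, and model of care is entered as one categorical variable. A reader could take it that factors are selected and their levels merely inspected. This stands as a caveat. But the sentence on assessing levels individually directly follows the removal rule, and nothing keeps levels together, so level-by-level removal remains the natural reading.

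**The classes come from a tree.** The abstract and the section on statistical analysis methods assign the classification to classification and regression trees. If phase enters the tree as one factor, the tree chooses its own splits and the reference is irrelevant. Using each cost driver once fits a whole factor better than separate dummies. This objection stands and limits the point. The regression comes before the tree, so the tree might receive pruned levels, but the text shown does not say which, and the two figures that might are not available.

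**The simulation is a simplification.** It uses one factor, normal errors and no covariates, and it omits the bootstrap iterations and the R² ranking. The figure of 98% is a worst case over four references, including ones an analyst might rarely choose. This also stands. The percentages are illustrations; the dependence on the reference is algebraic.

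**A reference level is a detail for the analysis plan.** Its absence alone would be no finding. The point rests on the selection method that the article does state, and naming a reference would not cure it.

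**Conclusion.** The point holds in limited form. As written, the selection rule lets an arbitrary coding choice decide which levels of phase of illness and model of care survive, and so which coefficients are reported. Between two plausible references the surviving grouping differed in about 54% of data sets in the main scenario, and in about 7% when only dying costs more. Both figures rest on assumed shares, assumed means, a 5% threshold and a single-factor linear model at 304 episodes per setting. No figure was computed for model of care, whose levels are not yet defined.

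Two stronger conclusions might be inferred and are not supported. One is that analysts using different references would end with different final casemix classes. That requires the tree to work on pruned dummies, which the documents do not establish, and no tree was run in the check. The other is that phase of illness could easily be lost as a criterion. Keep-or-drop of the factor agreed across all four references in about 95% of simulated data sets. This also means that the article's criterion-level comparison with the Australian classification is little affected for phase.

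**What to change.** Reword the dummy-variable sentence under Model development along these lines: phase of illness and model of care will each be kept or dropped as a whole factor, by a joint (multi-df) Wald or likelihood-ratio test or by the factor's total R² contribution; a retained factor is passed whole to the tree, which decides which levels to merge; estimates for individual levels may be reported descriptively, with the reference level named.

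Neither the joint test nor the tree's splits on a whole factor depend on the reference. The cost is about one sentence of analysis wording. No data collection or sample size figure changes.
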